#### 3. Håndgrebs styrke over-ekstremitet - Jamar dynamometer (Robert HC et al. 2011)

The Jamar dynamometer (Preston, MI, USA) er et justerbart håndtag som kan måle håndgrebsstyrke.

Håndgrebsstørrelsen kan justeres fra 2.5 til 7.5cm. Denne type håndgrebs-dynamometer udbredt i rehabilitering men er ikke en standard anvendt test. Procedure gennemføres siddende med albue bøjet i 90 grade og underarmen støttende på et armlæn. Patienten bliver instrueret til at klemme så hårdt som muligt om håndgrebet i 3-5 sekunder. Proceduren gennemføres tre gange med hver hånd med 10-20sekunders pause imellem hvert håndgrebsforsøg.

#### 4. Fysisk funktion – five-time- sit-to-stand-test (5T-STST) (Jones SE et. 2014)

Tiden på at rejse-sætte-sig er et inddirekte måling af eksplosiv muskelkraft af benene.

Testen udføres fra en stol med ryglæn og en sædehøjde svarende til 45-47 cm. Deltageren blive instrueret i at rejse og sætte sig 5-gange så hurtigt som muligt med armene krydset over brystet.

Tiden brugt på 5- rejse-sætte-sig registres. Testen gentages to gange for at indfange evt. læringseffekt. Der holdes en pause på 5-minutter imellem de to forsøg. Det bedste test-resultat anvendes.

Scoren "nul repetitioner" skrives hvis en patient ikke kan gennemføre testen (dvs. rejse-sætte-sig fra en stol uden brug af arme/hænder)

5. Statisk og dynamisk balance - (stående balance og 3-meter gang test) (Mequita R et al. 2016 and Guralnik JM et al. 1994)

a) Stående balance testes ud fra tre forskellige positioner (Statisk balance):

- Stående med samlede fødder
- Stående i semi-tandemstand (forreste fods hæl ved siden af bagerste fods storetå)
- Stående i tandemstand (forreste fods hæl foran bagerste fods storetå)

Instruktioner:

Patient skal være i stand til at stå uden brug af krykkestok eller rollator-

*"Jeg vil gerne teste din stående balance i forskellige stillinger, jeg viser dig nu hvilke og hvordan".*

*"Lad mig understrege at du kun skal kun udføre stillingen hvis du føler dig tryk ved det".*

*"Føler du dig tryk?" og "har du nogen spørgsmål?"*

Den sundhedsprofessionelle stå ved siden af patienten når testen gennemføres.

Tiden er afgørende under scoring af testen og hver position skal maksimalt holdes i 10 sekunder. Et sekund svarer til et point. Der kan scores mellem 0-30 point. Testpersonens samlede score udgøres af summen af de trin, der bliver gennemført.

- En score på 10 point, viser at personen fuldførte første position med samlede fødder og der fortsættes til semi-tandemstand.
- En score på 20 point viser, at personen fuldførte positionen med samlede fødder, og deslige fuldførte anden position semi-tandemstand. Kun hvis personen kan stå i semi-tandemstand i 10 sekunder gennemføres sidste position, tandemstand.
- En score på 30 viser, at testpersonen kan stå i alle tre positioner i 10 sekunder.

b) 3-meter gang test (dynamisk balance)

Testen vurderer den intuitive normale gang hastighed hos patienten. Der anvendes gangredskab hvis det anvendes under dagliggang.

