#### **3.4 Criteria for participation**

##### **3.4.1 Inclusion criteria**

- Indication for pulmonary rehabilitation according to national guidelines
- Unable to access and participate in the conventional out-patient hospital- or community-based PR when offered during routine consultation
- A post-bronchodilator ratio FEV1/FVC <70% (confirmed physician diagnosis of COPD)
- A post-bronchodilator FEV1 <80% (degree of airway obstruction) corresponding to GOLD grade 2-4 (moderate to very severe)
- GOLD group B, C, D corresponding to severe respiratory symptoms and/or frequent acute exacerbations

- Able to stand up from a chair (height 44-46cm) and walk 10 meters independently (with or without a walking aid)
- Able to lift both arms to a horizontal level with a minimum of 1 kilogram's dumbbells in each hand

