### **3.5.4 Physical function outcomes (baseline and at all follow-up visits)**

- ActivePAL triaxial accelerometer (PAL) – (Physical activity)
- 6-minute walk test (6MWT) – (walking capacity)
- 30-second sit to stand (30-sec-STS) – (leg muscle strength)
- Short Physical Performance Battery and (SPPB) – (function and frailty)
- Hand-grip strength (Jamar dynamometer) – (muscle strength upper extremity)

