### *Fysisk præstations målinger:*

#### 1. 30sec- sit-to-stand-test (30STS) (Jones CJ et. 1999) (standard test i Lunge-rehabilitering)

30-sec sit-to-stand test (30sec-STST) er en indirekte måling af muskelstyrke af benene.

Testen udføres fra en stol med ryglæn og en sædehøjde svarende til 45-47 cm. Deltageren blive instrueret i at rejse og sætte sig så mange gang som muligt på 30 sekunder med armene krydset over brystet. Antal gennemførte rejse og sætte sig bliver registeret. Scoren "nul repetitioner" skrives hvis en patient ikke kan gennemføre testen (dvs. rejse-sætte-sig fra en stol uden brug af arme/hænder). Testen gentages to gange for at indfange evt. læringseffekt. Der holdes en pause på 5-minutter imellem de to forsøg. Det bedste testresultat anvendes. Testen anvendes som **standard test i Lunge-rehabilitering og i ambulant medicinsk behandling.**

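### The timed five-times sit-to-stand scores inability in repetitions, the rule of the 30-second count test, and defines no value, category or rank on its own seconds scale

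*Protocol*

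**What the plan says.** Appendices 2, item 4 of the protocol (in Danish) asks the patient to rise and sit "5-gange så hurtigt som muligt med armene krydset over brystet", five times as quickly as possible with arms crossed. What is recorded is a time: "Tiden brugt på 5- rejse-sætte-sig registres". On attempts it says "Testen gentages to gange for at indfange evt. læringseffekt", and then "Det bedste test-resultat anvendes", so the best result counts. For inability it says "Scoren 'nul repetitioner' skrives hvis en patient ikke kan gennemføre testen", and a bracket explains this as being unable to rise and sit without using arms or hands.

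Appendices 2, item 1 gives the 30-second sit-to-stand the same inability sentence. There the recorded quantity is a count: "Antal gennemførte rejse og sætte sig bliver registeret".

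Section 3.4.1 requires a participant to be "Able to stand up from a chair (height 44-46cm) and walk 10 meters independently". A walking aid is allowed, and use of the arms to rise is not mentioned.

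Among physical function outcomes, section 3.5.4 lists the 30-second test and the "Short Physical Performance Battery and (SPPB) – (function and frailty"). It does not list the five-times test by name, and neither do Table 1 and Table 2.

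**The concern.** A timed test of a fixed five rises produces no repetition score. The inability sentence therefore gives an answer in a unit that the test does not use. Taken as a bare number, zero is the worst value on the 30-second test and the best conceivable value on a time scale. The protocol offers nothing else for these patients.

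The patients affected are the weakest. Entry requires standing up from a chair but does not rule out pushing up with the arms, while the test fails anyone who needs them. Inability can also develop later, since physical function is tested at weeks 10, 35 and 75. If the share unable differs between arms, the way the zero is handled can move the comparison, and it would favour the arm with more failures. Section 6.2 says that source data go directly into the e-CRF, and no separate source is described that would later tell a coded zero from a time.

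**Working it through.** The protocol gives no mean, SD, minimal important difference or power for the five-times test, so there is no stated figure to reproduce. The check compares the two rules and then follows each way in which the entry could be handled.

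**The two tests side by side (Appendices 2)**

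| | 30-second test (item 1) | Five-times test (item 4) |
|---|---|---|
| Recorded | number of completed rises | time for five rises |
| Better is | higher | lower |
| Attempts | two, best used | two, best used |
| Inability | zero repetitions | zero repetitions |
| Position of zero as a number | worst | best |

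The rule fits the left column only.

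**Route 1: the zero is stored in a seconds field.** Take one patient who finishes in 12 s, one who finishes in 20 s and one who cannot do the test. The stored values are 12, 20 and 0, and the unable patient ranks first. In the change analysis of section 3.6.1, a patient who finished in 16 s at baseline and later became unable would show a change of 0 − 16 = −16 s, a large false improvement.

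For arm means, let p be the share unable and T the mean time of completers, taken as equal in both arms. Neither is in the documents; both are assumed, with T from 12 to 20 s.

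- Arm mean with zeros = (1 − p) × T + p × 0 = T − pT, a shift of −pT.
- Bias in intervention minus control = (p_control − p_intervention) × T.

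| Unable: control / intervention | T = 12 s | T = 16 s | T = 20 s |
|---|---|---|---|
| 5% / 5% | 0 s | 0 s | 0 s |
| 10% / 5% | 0.05 × 12 = 0.6 s | 0.05 × 16 = 0.8 s | 0.05 × 20 = 1.0 s |
| 15% / 5% | 0.10 × 12 = 1.2 s | 0.10 × 16 = 1.6 s | 0.10 × 20 = 2.0 s |

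A positive value makes the intervention look slower than control. If the larger share unable were in the intervention arm, the sign would reverse. With 5% unable in both arms the difference is unbiased, but both means are 0.6 to 1.0 s too low. These are simple mean shifts, before the covariate adjustment of section 3.6.1.

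**Route 2: the entry is treated as missing.** Section 3.6.1 regards all data as missing at random and relies on the likelihood to handle the gaps. Here the value would be missing because the patient cannot perform the test, which is itself a result on the outcome. The arm with more failures would lose more of its weakest performers, and the model can recover only what covariates and observed values predict.

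**Route 3: the entry is kept as a separate 'unable' category.** The zero-as-time bias does not arise. The protocol does not specify this route, and it would still need a rank or category for those patients.

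**The case against.** The strongest reply is that the protocol says zero repetitions and never 0 seconds. An entry in another unit can be read as a flag for inability, and it misleads only if someone puts it in a seconds field and analyses it. This stands. A reader might infer that patients who cannot do the test will enter the data as the fastest, but the text does not say so. That outcome is conditional.

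A reader might also infer that one failed attempt would beat a valid time under the best-of-two rule. The documents do not support this. The rule applies to a patient who cannot do the test without arms, so a patient with one completed attempt does not trigger it. The protocol also speaks of the best result, not the smallest number.

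The reach is limited too. No passage says that mean five-times sit-to-stand seconds will be compared between arms. The test may serve only as part of the SPPB/Guralnik test, whose chair-stand scoring is not given. Table 2 gives the unit for the row holding the Guralnik test as seconds, but it also states that the first entry in that row's power column is not established. Entry requires rising from a chair of 44 to 46 cm, close to the 45 to 47 cm test chair, so inability may be uncommon; its frequency is unknown.

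Finally, the ranking of unable patients in the analysis could be left to a statistical analysis plan or the e-CRF specification. That is fair for the analysis detail. It does not excuse a scoring rule that the protocol does state and that does not fit its own scale.

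**Conclusion.** The concern holds as a minor, conditional defect. The inability score in Appendices 2, item 4 is in the wrong unit for a timed outcome, matches the rule of the count test, and leaves patients who cannot do the test without a time-scale value, category or rank. Entered as a time, the zero would place them first; treated as missing, it would fall under an assumption that does not suit it.

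No size can be drawn from the documents. The figure of 0.6 to 1.0 s per 5 percentage points is an illustration that needs three things: zeros stored as seconds, assumed completer means of 12 to 20 s, and an assumed difference in the share unable. With equal shares there is no between-arm bias. Without a stated SD or important difference for this test, the shift cannot be called large or small. The primary outcome and the 30-second test are not affected.

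**What to change.** Replace the inability sentence in Appendices 2, item 4, and leave it in item 1, where it is correct. The new text should state three things:

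1. A patient who cannot do the test is recorded under a separate 'unable' code, never as a number in the seconds field.
2. The best result is the shortest time among completed attempts.
3. In the analysis, unable patients are ranked worst, or given the lowest category if the test is scored in categories.

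The same edit should say whether the five-times test is analysed in seconds or used only within the SPPB.

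The cost is a short text change in the appendix and one e-CRF code, with no effect on sample size or visits. It costs least if made before data entry. If entries already exist, any zero in the time field should be checked and recoded while the analyst is still blinded.

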**Instruktion:**

1. Dette er gang distancen på 3 meter du skal (viser af sundhedsprofessionel). Du skal nu gå fra denne afmærkning til (vises) til den anden ende 3 meter fremme. Du skal gå i dit vanlige gangtempo, ligesom hvis du gik udenfor på gaden
2. Den Sundhedsprofessionelle viser hvordan.
3. "Går hele vejen forbi markeringen 3 meter fremme før du stopper. Jeg går lige bagved dig. Føler du dig tryk ved testen?"
4. Hav patienten stående med fødderne ved startmarkering.
5. Du skal starter efter kommandoen parat-gå.
6. Tiden på stopuret starter når patienten begynder at gå

7. Den Sundhedsprofessionelle går bagved patienten

8. Tiden stoppes når fødderne krydser slutmarkering 3 meter fremme.

### **Selvrapporteret målinger:**

Patients modtager en kort instruktion om skemaerne og udfylder dernæst spørgeskemaerne i et uforstyrret rum uden involvering af den sundhedsprofessionelle person.

#### 1. Selvrapporteret luftvejssymptomer - COPD Assessment Test (CAT) (**standard test i Lunge-rehabilitering**)

COPD Assessment Test (CAT) består af otte spørgsmål der omhandler patient-oplevede respirations symptomer nu og her. Hvert spørgsmål scores fra 0-5 (0 indikere ingen symptomer, 5 værst tænkelige symptomer) der summeres til en samlet score fra 0-40 point. Skemaet er **standard skema i lunge-rehabilitering og i ambulant medicinsk behandling**.

#### 2. Selvrapporteret angst og depression symptomer - Hospital Anxiety and Depression Scale (HADS) (**standard skema i Lunge-rehabilitering**)

Hospital Anxiety and Depression Scale (HADS) består af 14 spørgsmål omhandlende dagligdags situationer som giver anledning til bekymring, angst og nedtrykthed. Spørgeskemaet består af to subscore angst-symptomer (syv spørgsmål) og depressions symptomer (syv spørgsmål). Hvert spørgsmål scores fra 0 to 3 (0 = no symptoms). Skemaet er ikke et diagnostisk redskab.

#### 3. Selvrapporteret livskvalitet – Euro-QoL (EQ-5D-3L)

Europ-QoL er et standardiseret spørgeskema. Skemaet anvendes i flertallet af danske befolkningsundersøgelser til at kvantificere den helbredsrelaterede livskvalitet og funktionsevne ud fra en subjektive vurdering. Det således muligt både at vurdere effekten af en behandling på krops- og aktivitetsniveau samt sammenligne med baggrundsbefolkningens generelle helbredstilstand.

#### 4. Selvrapporteret muskel og skelet smerter – Brief Pain Inventory (BPI)

Brief Pain Inventory registrerer patientens oplevede smerter indenfor den seneste uge. Der spørges til smerte intensitet, lokalisation af smerter i kroppen, effekt af smertelindrende medicin (0-100%), samt smerte geners indvirkning på daglige aktiviteter, humør, evne til at gå, passe arbejde, forhold til sociale relationer.

#### 5. Selvrapporteret træthed og udmattelses symptomer – Multidimensional Fatigue Inventory (MFI-20)

MFI-20 afdækker fem dimensioner af træthed: Generel træthed (General fatigue), Fysisk træthed (fysisk fatigue), Mental træthed (Mental fatigue), Nedsat motivation (Reduceret motivation) og Nedsat aktivitet (Reduceret aktivitet). Der stilles 20 spørgsmål ex. ”Jeg føler mig træt”, og patienten bedes om at indikere i hvilken grad udsagnet er korrekt på en fem-punkts-skala fra (ja, det er rigtigt - Nej, det er ikke rigtigt).

Spørgeskemaet har til hensigt at måle træthed som en tilstand, følsom over for midlertidige ændringer, og patienten besvarer spørgeskemaet på baggrund af hvordan de har haft det i den senere tid.
